We hypothesize that these three additive training implementation strategies will predict respective graduated increases in implementation success at 4-, 8-, 12-, and 24-months post-training (see Figs. 1 and [67]). That is, we predict that reach, effectiveness, adoption, implementation, and maintenance will be higher in the Local Supervision condition relative to the Direct Training condition and that the Direct Training condition’s implementation outcomes will be higher than the Materials Only condition. Drawing on theories of organizational [68, 69] and provider [70–73] change, we also hypothesize that organizational (e.g., shared norms of the importance of EBP) and provider (e.g., self-efficacy for EBP delivery) factors will mediate the stronger impact of the more intensive training strategies on implementation success and client mental health outcomes. To facilitate this latter aim, in a subset of 15 LGBTQ community centers (five centers per condition), we will compare the three training implementation strategies in terms of client mental health symptom change from before implementation to 4, 8, 12, and 24 months after.

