### Randomization

Upon receiving 90 signed memoranda of understanding, the 90 LGBTQ community centers will be randomized in a 1:1:1 ratio to receive one of the three implementation strategies. Randomization will be stratified by director report of anticipated staff participation. Specifically, high-attendance centers will be operationalized as those with greater than the median number of anticipated providers across the 90 enrolled centers whereas low-attendance centers will be operationalized as those that anticipate fewer than the median number of providers per center. Centers whose anticipated number of providers is at the median will be randomly and evenly divided across the two groups. The 15 effectiveness centers will be randomized separately to ensure their equal distribution across the three implementation strategies. Randomization allocation will be generated by the study statistician and assigned by the study coordinator. All participants and study staff will be unmasked to condition assignment, as necessitated by the study design.

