### Implementation outcomes

In Aim 1, we will assess the implementation success of three LGBTQ-affirmative CBT implementation strategies across the 90 LGBTQ community centers. The primary implementation outcome is provider fidelity to LGBTQ-affirmative CBT using our validated “simulated practice” assessment [64]. Providers will watch two brief (3-minute) video clips of an SGM actor roleplaying a presenting concern and then briefly describe in writing the clinical approaches they would use to address the concern. Research assistants will then code responses to assess participants’ application of LGBTQ-affirmative CBT skills using our reliable (ICC = 0.87) and valid rating scheme (57). Secondary implementation outcomes include mixed-methods assessments of the reach, adoption, familiarity, modification, and maintenance of LGBTQ-affirmative CBT skills across centers (See Table 1 for operationalizations).

**Table 1 Tab1:** Measures

Outcomes	Measures	Data Source	Time point
Primary outcomes			
Implementation fidelity	∙ Simulated practice assessment [57] based on previous EBP research [117–120].	Provider simulated practice assessment	baseline, 4 m, 8 m, 12 m, 24 m
Secondary outcomes			
Reach	∙ Percentage of active clients who receive the EBP will be self-reported in provider surveys. Semi-structured qualitative interviews with providers will highlight reasons for stronger or weaker reach.	Provider surveys and qualitative interviews	4 m, 8 m, 12 m, 24 m
Adoption	∙ Percentage of providers who self-report practicing LGBTQ-affirmative CBT out of total who were trained. Semi-structured qualitative interviews with providers will highlight why and in what cases providers chose not to implement.	Provider surveys and qualitative interviews	baseline, 4 m, 8 m, 12 m, 24 m
Implementation	∙ Confidence with and use of LGBTQ-affirmative CBT skills will be measured using a scale adapted from the Counselor Activity Self-Efficacy scale [121] and Use of LGBTQ-affirmative CBT skills scales [57]. ∙ Modification of LGBTQ-affirmative CBT will be assessed by the Modification and Adaptation Checklist [122] and semi-structured qualitative interviews with providers.	Provider surveys and qualitative interviews	baseline, 4 m, 8 m, 12 m, 24 m

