### Data collection, management, and analysis

Mental health provider, director, and local supervisor participants will complete baseline and follow-up surveys via Qualtrics. Client surveys will be administered and stored on REDCap. All participant consent, contact, tracking, and scheduling information will be recorded in REDCap.

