#### Provider implementation fidelity outcome analyses

We will summarize provider characteristics (e.g., volunteer status, length of SGM service) overall and by implementation strategy and assess for baseline imbalances. We will then compare the implementation outcomes for the Materials Only condition vs. Direct Training vs. Local Supervision. The primary implementation outcome is provider implementation fidelity (assessed via simulated practice responses) at 8-month follow-up; secondary outcomes include 8-month provider self-efficacy, competency, familiarity, and use of LGBTQ-affirmative CBT. For primary and secondary outcomes, will use mixed effects models [93] with the identity link function to compare the effect of implementation strategies. The fixed effects include the time effect and the time × implementation strategies interaction terms; the random effects include center and within-provider repeated measures. We will use the robust score test to assess whether the interaction terms are significantly different across the three strategies, with a 0.05 overall Type I error rate, and a 0.025 error rate for each of the two primary strategy comparisons. For secondary outcomes, we will compare implementation strategies with a 0.05 Type I error rate. We will re-run these analyses with 12- and 24-month outcomes to determine implementation maintenance.

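### The masking rule unmasks all study staff as a necessity of the design, but the design does not require it for the research assistants who score the primary outcome

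*Protocol article*

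**What the plan says.** All references are to the protocol article.

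- **Masking (Randomization).** "All participants and study staff will be unmasked to condition assignment, as necessitated by the study design". No exception is made for outcome coders here or elsewhere.
- **What is scored, and by whom (Implementation outcomes).** Providers watch two short clips and "then briefly describe in writing the clinical approaches they would use to address the concern". "Research assistants will then code responses to assess" the application of the taught skills, "using our reliable (ICC = 0.87) and valid rating scheme (57").
- **Role of the score (Provider implementation fidelity outcome analyses).** "The primary implementation outcome is provider implementation fidelity (assessed via simulated practice responses) at 8-month follow-up". Type I error is split as "a 0.025 error rate for each of the two primary strategy comparisons".
- **How answers are collected (Data collection, management, and analysis).** "Mental health provider, director, and local supervisor participants will complete baseline and follow-up surveys via Qualtrics".
- **Expected direction (Background).** The team predicts that "these three additive training implementation strategies will predict respective graduated increases in implementation success", that is, Materials Only below Direct Training below Local Supervision.
- **Identifiers (Ethical considerations).** Participants get unique study numbers, and survey data are kept apart from identifying information. The section does not mention condition or time point.

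**The concern.** Scoring a free-text answer against a skills scheme takes judgement. A coder who knows that an answer comes from the most intensive arm at a follow-up visit may score it more generously, without intending to. The team has published a graded expectation, so any such lean would probably run in the direction that the trial is testing.

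The article is not merely silent on this. It states a universal rule and gives a reason, and the reason does not reach the coders. Providers know what training they receive, trainers know whom they teach, and the coordinator assigns the allocation. A person reading a paragraph of text needs none of this knowledge.

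The one safeguard stated is the scheme's reliability and validity. An ICC of 0.87 measures how far raters agree, and raters who share an expectation can agree closely and still be wrong in the same direction.

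The score also reaches beyond the primary comparison. Eight-month fidelity is the main outcome of the moderation analysis, the outcome of the first mediation model, and an intermediate in the client PHQ-9 mediation model.

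**Working it through.** **Inputs** (Sample size justification for fidelity, unless noted)
- Direct Training change from baseline to 8 months: 0.14; variance 0.0439.
- Detectable effect at 80% power: d = 0.34–0.46, with ICC ≤ 0.1.
- Error rate 0.025 per comparison. Sidedness is not stated; two-sided is assumed here.
- 90 centers, so 30 per arm, with about 6 providers each.
- Size of any coder lean: not in the document, so a range is assumed.

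**Step 1. The plan's own figures.**
- SD of change = sqrt(0.0439) = 0.2095. Standardized change = 0.14 / 0.2095 = 0.668, which matches the stated 0.67.
- Detectable d = (z[0.9875] + z[0.80]) × sqrt(2 × (1 + (m − 1) × ICC) / (30 × m)). With m = 6 and no loss this gives 0.325 at ICC 0 and 0.398 at ICC 0.1. The stated lower end of 0.34 is met at ICC of about 0.01–0.02. The upper end of 0.46 at ICC 0.1 needs about 30–35% loss, which this section does not state. The range is plausible, and it is used below only as a yardstick.

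**Step 2. The yardstick in raw points.**
- 0.34 × 0.2095 = 0.071
- 0.46 × 0.2095 = 0.096

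**Step 3. Assumed leans set against the yardstick.** Each is an assumed difference between adjacent arms in the *change* score, so the lean must differ by both arm and time point.

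The last column is the chance of rejecting when there is no true difference. It uses SE = d / (2.241 + 0.842), which is 0.149 for d = 0.46 and 0.110 for d = 0.34. The probability is 1 − Φ(2.241 − b/SE) + Φ(−2.241 − b/SE), where b is the lean in SD units.

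| Assumed lean (points) | In SD units | Share of detectable effect | Rejection under no true difference (nominal 0.025) |
|---|---|---|---|
| 0.01 | 0.05 | 10–14% | 0.033–0.039 |
| 0.02 | 0.10 | 21–28% | 0.057–0.085 |
| 0.05 | 0.24 | 52–70% | 0.26–0.47 |

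The shares are 0.01/0.096 to 0.01/0.071, and likewise for the other rows, computed from unrounded values. The largest lean is over a third of the whole expected Direct Training change (0.05/0.14 = 36%), so it is the far end of the range and not a central estimate.

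**Step 4. When a lean cancels.** A lean that raises one arm's scores equally at baseline and 8 months drops out of a change score. The analysis model lists time and time × strategy as fixed effects, with no strategy main effect, so cancellation there may be only partial. Full bias needs a lean that depends on arm and time point together.

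**The case against.** **Unmasked staff is not the same as unmasked coding.** The masking sentence sits under Randomization and can be read as describing knowledge of center allocation. Coding from text under a study number would be compatible with the article, and the detailed coding procedure may sit in the full protocol or in the cited rating scheme. This stands in part: the article does not show that coders know the arm when they score. But a study number does not by itself hide condition or time point, and masked coding would still conflict with the sentence as printed.

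**A reader might infer that the coders do score with knowledge of condition and that the graded result would be their product.** The documents do not support this. They say nothing of what coders see, and they give no evidence of a lean or of its size.

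**A reader might also infer that the damage would be beyond repair.** It would not be. The outcome is stored text, so masked coders can re-score it at any time, which would be impossible for a rating made by live observation.

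**Masking may be imperfect.** Answers may reveal what training the provider received. This is true and limits the benefit, but it is no reason to leave coders unmasked by rule.

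**Conclusion.** The point holds as a wrong statement in the plan. The rule that all staff are unmasked because the design demands it is not justified for coders of the primary outcome, and the stated agreement statistic does not fill the gap.

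The consequence is a possible detection bias in the hypothesized direction, not a demonstrated one. Under assumed leans of 0.01 to 0.05 points that differ by arm and time point, it would amount to between 10% and 70% of the detectable effect. That span reflects the assumption and should not be quoted as an estimate. A lean equal at both time points would largely cancel. The calculation further assumes two-sided tests and standard errors implied by the plan's own detectable effects.

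The change is worth making because it protects the single primary endpoint without touching N, design or power.

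**What to change.** 1. In Randomization, replace the masking sentence with: *Participants, trainers and coordinators are unmasked; coders of the simulated practice responses are masked to condition, center, participant and time point.*
2. In Implementation outcomes, state that responses are exported under a random ID, stripped of identifying phrases, mixed in random order across arms and time points, and coded by research assistants without access to the allocation. The article does not describe the assistants' other duties, so the sponsor should confirm that such staff are available.
3. If any responses have already been coded unmasked, re-score them masked from the stored text.
4. If masked coding already takes place, only the wording needs correcting.

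The cost is a protocol wording change and a small data-management step, plus coder time if re-scoring is needed. Some answers may still hint at the training received, and this should be acknowledged as a limitation.

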### Participants

This trial involves four classes of participants: directors (Aims 1–3), mental health providers (Aims 1–3), local supervisors (Aims 1–3), and clients (Aim 3).

#### Directors

Upon randomization, each of the 90 centers will be asked to nominate an individual to complete a director survey at baseline. Directors must be 18 years or older and in a clinical director, executive director, or similar leadership role at a participating LGBTQ community center. Directors may be double-enrolled as providers (i.e., participating in the training) and/or local supervisors and will be asked to complete survey questions for each of their roles at each time point. Directors will be contacted via email to complete follow-up [77] surveys at 4-, 8-, 12-, and 24-months post-baseline. In the event that a director leaves their position, they will be asked to nominate a new director at the center who will be invited to enroll in the study and complete all subsequent follow-up surveys.

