### Center enrollment

We have partnered with CenterLink, an international nonprofit organization and network of LGBTQ community centers. At least 200 CenterLink-affiliated centers provide mental health services, and others offer referrals to local mental health providers [55]. We will send targeted email communications to directors of these centers, informing them of this trial and training opportunity. Centers are eligible to enroll in this trial if they are (1) a current member of the CenterLink network, (2) based in the United States, and (3) anticipate at least two providers associated with their center participating in the training/study. Directors at centers that meet these criteria will sign a memorandum of understanding to officially enroll their center into the trial. We aim to enroll 90 centers.

In addition, 15 of the 90 enrolled centers will be selected to participate in Aim 3 of the study, in which they will additionally be asked to facilitate the collection of client mental health data at baseline and through the 24-month follow-up through activities such as distributing information about the survey to their mental health clients. These 15 centers were selected a priori to represent diversity across geographic region, budget, and populations served. Shortly before client data collection begins, these centers will be mailed palm cards containing client recruitment text alongside instructions regarding how to introduce the survey to clients.

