#### Local supervisors

Upon randomization, centers randomized into the Local Supervision condition (described below) will be asked to nominate an individual to serve as the local supervisor, who will champion the supervision, training, and sustainment of LGBTQ-affirmative CBT at their center. The local supervisors should have significant therapeutic experience and be comfortable and interested in (1) learning how to oversee other providers at their center as they learn to deliver LGBTQ-affirmative CBT and (2) training future mental health providers to deliver LGBTQ-affirmative CBT. Local supervisors will be asked to attend an additional 12-week LGBTQ-affirmative CBT leadership workshop following the conclusion of the live webinar trainings, in addition to answering survey questions at all five assessment time points. To be eligible to attend the leadership workshop, local supervisors must provide consent and complete the baseline survey. Local supervisors may be simultaneously enrolled as directors and/or providers.

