Maintenance	∙ Funding stability, environmental support, organizational capacity, and strategic planning will be measured by the Program Sustainability Assessment Tool [123] and semi-structured qualitative interviews with providers and directors.	Director surveys, provider surveys and qualitative interviews	4 m, 8 m, 12 m 24 m
Implementation determinants			
Inner setting	∙ Motivation for change, resources, and staff attributes will be measured by subscales of the Organizational Readiness for Change– Treatment Staff Version and Organizational Readiness for Change– Treatment Director Version [124].	Director surveys, provider surveys	baseline, 4 m, 24 m
Outer setting	∙ SGM Policy Climate (e.g., anti-LGBTQ laws/policies) will come from existing policy and attitudinal indices [35, 55, 125] linked to the municipality of each center. ∙ Community socioeconomic disadvantage and rurality (e.g., poverty, housing characteristics, unemployment, education) will come from the American Community Survey [126] and be linked to the county of each center. ∙ Mental health workforce characteristics (e.g., provider prevalence in each state, continuing education requirements of centers’ states) will derive from existing metrics [127]. ∙ Semi-structured qualitative interviews with providers and directors will inform assessment of the outer setting.	Secondary data, provider and director qualitative interviews	baseline
Intervention characteristics	∙ Directors’ and providers’ openness to adopting EBPs and perceived divergence between EBPs and current practice will come from the EBP Attitude Scale [128].	Director and provider surveys	baseline, 4 m, 24 m
Individual characteristics	∙ Provider, director, and client demographics (e.g., race/ethnicity, sexual orientation, gender) will be assessed via self-report questionnaires.	Provider, director, and client surveys	baseline, 4 m, 8 m, 12 m 24 m

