#### Mediation analyses

We will assess client mental health as a function of our three implementation strategies as mediated through provider and organizational targets. We hypothesize that organizational (e.g., norms about LGBTQ-affirmative CBT) and provider (e.g., LGBTQ-affirmative CBT self-efficacy) targets will mediate the impact of implementation strategies on implementation success, and further on client mental health. We will use the difference approach [101] for multilevel mediation [102] of center-level implementation strategy on 8-month follow-up provider-level implementation fidelity through our hypothesized organizational and provider targets measured at 4-month follow-up. We will parse the implementation strategies’ total effect on the implementation outcome into direct and indirect (mediated) effects. Specially, we will fit a mixed-effects model of the implementation strategies on implementation outcome for the total effect and fit another mixed-effects model of the implementation strategies on implementation outcome plus center-level targets and provider-level targets. The fixed effects of the first model include the implementation strategies, baseline implementation fidelity, and baseline organizational and provider targets, and the second model replaces baseline organizational and provider targets with 4-month follow-up targets; random effects include center. The indirect effect is the difference between the estimated coefficients of implementation strategies between the two models; significance will be tested using bootstrapping [103]. We will use the same multilevel approach to test mediation of the association between implementation strategy and 12-month follow-up client-level PHQ-9. We will fit two mixed-effects models to estimate the total, direct and indirect (mediated) effects. The fixed effects of the first model include the implementation strategies, baseline PHQ-9, baseline implementation fidelity, and baseline organizational and provider targets, and in the second model, the baseline organizational and provider targets are replaced with 4-month follow-up targets and baseline implementation fidelity is replaced with 8-month follow-up implementation fidelity; the random effects include center and provider. We will re-run these analyses with 24-month follow-up PHQ-9 to determine maintenance of effects.

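### Director baseline scores are collected after unmasked randomization, so the readiness, attitude, climate and leadership values used in the moderation and mediation analyses can already carry a reaction to the allocation

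*Protocol article*

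**What the plan says.** Before randomization, directors are already in contact with the study. Under Center enrollment, "Directors at centers that meet these criteria will sign a memorandum of understanding to officially enroll their center into the trial". They also supply data at that stage, because under Randomization, "Randomization will be stratified by director report of anticipated staff participation". Allocation follows once every center has signed: "Upon receiving 90 signed memoranda of understanding, the 90 LGBTQ community centers will be randomized in a 1:1:1 ratio". Nobody is masked: "All participants and study staff will be unmasked to condition assignment, as necessitated by the study design".

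The director survey comes afterwards. Under Directors: "Upon randomization, each of the 90 centers will be asked to nominate an individual to complete a director survey at baseline". Under Local supervisors, also at randomization, "centers randomized into the Local Supervision condition (described below) will be asked to nominate an individual to serve as the local supervisor", and these supervisors answer surveys at all five time points, baseline included.

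Table 1 lists director surveys as a baseline source for two groups of measures:
- **Determinants.** Under inner setting, "Motivation for change, resources, and staff attributes will be measured by subscales of the Organizational Readiness for Change". Under intervention characteristics, attitudes come from the EBP Attitude Scale.
- **Organization-level targets.** These are the Implementation Climate Scale subscales and the Implementation Leadership Scale.

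The determinants, with their interactions with strategy, are candidates in the stepwise models under Moderation analyses. The targets enter the models under Mediation analyses: "The fixed effects of the first model include the implementation strategies, baseline implementation fidelity, and baseline organizational and provider targets".

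**The concern.** These scales ask leaders how motivated and resourced the center is, how open they are to evidence-based practice, and how far the organization expects and rewards the new treatment. A leader who has just learned that the center gets digital materials only, or that it gets webinars and a year of supervision, may answer differently for that reason alone. The score is then partly a response to the assignment.

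The analyses treat it otherwise. Mediation adjusts for baseline organizational targets as if they preceded the strategy. Moderation may use baseline readiness and attitudes to say which strategy works in which kind of center, and the Dissemination section promises directors guidance of that type. Restricting moderators to the baseline wave would not help, because that wave is itself exposed. No later analysis can recover a pre-allocation value that was never measured.

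**Working it through.** The article gives no figure to reproduce. The check has three parts: the order of events, where the scores are used, and the direction of the bias.

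**1. Order of events**

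| Step | Section | Does the center know its arm? |
|---|---|---|
| Director signs memorandum and reports anticipated staffing | Center enrollment; Randomization | No |
| All 90 memoranda in; 1:1:1 randomization, unmasked | Randomization | Disclosure date not stated |
| Only Local Supervision centers asked for a supervisor | Local supervisors | Yes, 90 / 3 = 30 centers |
| Director respondent nominated, then surveyed | Directors | Yes for the 30; inferred for 90 − 30 = 60 |

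The request for a supervisor itself reveals the arm. A director who doubles as local supervisor answers for both roles at baseline and so cannot be unaware of it. No section withholds allocation until the director survey is in. Knowledge in one arm only is enough to create a difference between arms.

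**2. Where the scores are used**

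- Fidelity comparison (Provider implementation fidelity outcome analyses): fixed effects are time and time × strategy; random effects are center and provider. No director score.
- PHQ-9 comparison (Effectiveness outcome analysis): same structure. The sensitivity analysis adds client factors and center covariates such as rurality and size. No director scale is named.
- Moderation: readiness and attitudes are eligible.
- Mediation: baseline organizational targets are in the first (total-effect) model. The second model replaces them with 4-month targets.

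**3. Direction of the bias**

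*Mediation.* Let M₀ be the target before allocation and T the indicator for the more intensive of two strategies. Suppose Y = τT + βM₀, and the recorded baseline is M = M₀ + δT. Substituting M₀ = M − δT:

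Y = (τ − βδ)T + βM

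The total-effect coefficient becomes τ − βδ. The second model contains no baseline target, so its coefficient τ′ does not move by this route. The indirect effect is defined as the difference between the two coefficients:

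(τ − βδ) − τ′ = (τ − τ′) − βδ

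Both the total and the indirect effect therefore move by −βδ. If leaders react favorably to more support and higher scores go with better outcomes, both are understated. If leaders find the heavier arm burdensome, the sign reverses.

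*Moderation.* Suppose Y = τT + βR₀ + γTR₀, with recorded readiness R = R₀ + δT. In the arm with T = 1, Y = τ + (β + γ)(R − δ). A uniform reaction leaves the interaction slope alone but moves the strategy contrast at every readiness value by −(β + γ)δ, and so moves the point at which one strategy overtakes another. If the reaction also depends on prior readiness, so that R = (1 + λ)R₀ + δ when T = 1, the slope in that arm becomes (β + γ)/(1 + λ). An interaction then appears even when γ = 0.

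The documents give no β, γ, δ or λ, so no magnitude follows.

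**The case against.** The strongest reply is that the article fixes when the respondent is nominated, not when each center is told its arm. Materials Only and Direct Training centers could still be uninformed when the director answers. The provider flyers do not settle this, since the benefits listed under Mental health providers are not specific to an arm. This stands: a reader might infer that all 90 directors know their allocation, but the text makes this effectively explicit only for 30.

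A reader might also infer a threat to the primary result, for instance by setting an assumed bias against the detectable d = 0.34–0.46. The documents do not support that. Those values belong to a fidelity contrast that contains no director covariate, and any assumed shift and slope would be invented.

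Three further points stand in part:
- The Implementation moderators section draws on later waves as well as baseline, so director baseline values are not the sole designated moderators. They remain eligible, and they are explicit covariates in mediation.
- The signer of the memorandum need not be the survey respondent, so moving the survey also means moving the nomination.
- Readiness, attitudes, climate and leadership also have provider sources, and providers are recruited and surveyed after randomization. Moving the director survey is a partial cure, and the provider versions are no substitute for it.

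The affected analyses are not the confirmatory ones, and the Implementation and effectiveness mediators section calls the serial mediation exploratory. That limits the weight of the point but does not answer it.

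**Conclusion.** The point holds in limited form. As written, the director respondent is nominated and surveyed after unmasked randomization. At least the 30 Local Supervision centers know their arm by then, and nothing protects the other 60. Director-rated baseline readiness, attitudes, climate and leadership can therefore carry a reaction to allocation. This can bias the Aim 2 moderation models and the total-effect mediation models, and with the latter the indirect effect.

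The conclusion assumes that learning the arm changes some directors' answers and that those scores relate to outcome. Both are plausible and neither is quantified, so the size is unknown. The primary fidelity and PHQ-9 comparisons are unaffected. The change is worth making because it is cheap and because the center-specific guidance depends on clean moderators.

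**What to change.** Amend the Directors section along these lines: *Each center nominates its director respondent when it signs the memorandum. Once all memoranda are in, the respondent's consent and baseline survey must be received before the center is told its condition. Follow-up waves are timed from the common study baseline or training launch.*

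Collecting the surveys after the last memorandum, with follow-up on a common clock, keeps director waves aligned with provider waves rather than staggered over the enrollment period. The cost is an earlier nomination, re-ordering one online survey, and a short delay for slow responders. The article should also state that provider-rated versions of these scales remain post-randomization measurements.

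If allocations have already been released:
- Treat director-rated baseline scales as post-allocation.
- Report the mediation total effect also without adjustment for them.
- Label moderator findings based on them exploratory.
- Rest the Aim 2 guidance on facts fixed before allocation: policy climate, rurality, budget and anticipated number of providers.

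This fallback costs one extra model per mediation analysis and narrower claims about readiness and attitudes.
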